## **5. ASSESSMENTS**

The following assessments will be conducted at both baseline and follow-up, as feasible and subject to participant consent and willingness to participate in specific evaluations:

- (1) Demographic and clinical data collection: This includes a comprehensive collection of demographic and clinical data (e.g., age, sex, education, socioeconomic status, marital status, handedness, etc.), a physical examination, and standard laboratory testing (complete blood count and blood chemistry).

- (2) Traumatic event assessment: We will assess the types and timing of traumatic events experienced across the life span, using both quantitative and qualitative evaluation methods. This includes, but is not limited to, characterizing events by their nature (e.g., single-incident vs. repeated/chronic exposure), presence of physical injury, and age of first exposure.
- (3) Psychiatric evaluation: This involves a comprehensive evaluation of the participant's mental status, including PTSD, using standardized clinical interviews as Structured Clinical Interview for DSM (SCID) and the Clinician-Administered PTSD Scale for DSM (CAPS). Additionally, a battery of validated questionnaire will be utilized to measure various aspects of psychopathology, including depression, anxiety, alcohol use, smoking habit, suicide, resilience, anger, and impulsivity.
- (4) Multimodal brain imaging: This may include high-resolution T1-weighted imaging, proton magnetic resonance spectroscopy (1H-MRS), arterial spin labeling (ASL), resting-state functional MRI, and diffusion tensor imaging (DTI), which will be obtained using 3.0 Tesla MRI scanners. The specific imaging modalities used will depend on participant consent and feasibility of each scan.
- (5) Neurophysiological testing: This includes skin conductance response, and heart rate variability
- (6) Comprehensive neuropsychological assessment: A comprehensive neuropsychological assessment covering various cognitive domains will be conducted.
- (7) Peripheral blood biomarker analysis and genetic/epigenetic profiling

## **6. STATISTICAL ANALYSIS PLAN**

Statistical analysis will be conducted using a rigorous approach to examine both cross-sectional differences and longitudinal changes, as well as to identify associations between various measures.

### **6.1. General Principles and Methods**

- (1) Cross-sectional between-group comparisons: For continuous demographic variables, one-way ANOVA or t-test will be employed. Categorical variables will be compared using Fisher's exact test. For other cross-sectional comparisons of neuroimaging, clinical,

neurophysiological, and neuropsychological characteristics between groups, independent t-tests, chi-squared tests, or analysis of covariance (ANCOVA), or multiple linear regression analysis will be utilized, as appropriate. Potential covariates such as age, sex, and other relevant factors, will be considered, as necessary.

- (2) Longitudinal Analyses: To assess longitudinal changes in neuroimaging, clinical, neurophysiological, and neuropsychological measures, repeated measures ANCOVA or linear mixed-effects models will be employed. These models are robust for handling within-subject correlations and missing data inherent in longitudinal designs.
- (3) Assessment of Associations: Correlations between clinical severity, scale scores, and other assessment findings will be examined using Pearson's correlation or Spearman's correlation. To control for potential confounding variables and assess independent relationships, multiple linear regression or linear mixed-effects models will be used, as appropriate.
- (4) Neuroimaging-Specific Analyses:
  - Structural and Functional Brain Changes: We will compare and analyze structural and functional brain changes between groups.
  - MRS Neurometabolite Analysis: For the analysis of individual MRS neurometabolites, the LCModel or appropriate post-processing tools will be used.
  - Graphical Analysis and Presentation: For graphical analysis and presentation of brain imaging data, SPM (Statistical Parametric Mapping) and FSL (FMRIB Software Library), or other neuroimaging analysis softwares will be utilized.

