## **3. STUDY DESIGN**

This study is a naturalistic observational study involving adults and adolescents with and without trauma exposure. Participants will be recruited into trauma-exposed and trauma-unexposed groups.

At baseline, all participants will undergo comprehensive multi-modal neuroimaging, neurophysiological, clinical, and cognitive assessments. Follow-up evaluations will be conducted flexibly, adapting to the natural course of participant engagement and clinical needs. While we aim for periodic assessments, including potential evaluations around 3 months, 6 months, 1 year,

2 years, within 5 years, and within 10 years, the precise timing and frequency of these follow-ups will depend on individual participant availability and consent, reflecting the real-world nature of this study. The same protocols as baseline will be utilized for all follow-up assessments to ensure consistency.

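### Section 6.1 credits repeated measures ANCOVA, along with mixed models, with a robustness to missing data that it does not have, in a study whose visits and assessments are optional

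*Protocol*

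**What the plan says.** Protocol section 6.1 (2) names two methods for longitudinal change in the imaging, clinical, neurophysiological and neuropsychological measures: "repeated measures ANCOVA or linear mixed-effects models will be employed". It gives no rule for choosing between them. The next sentence justifies the choice: "These models are robust for handling within-subject correlations and missing data inherent in longitudinal designs".

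Section 3 describes the data these methods will meet. "Follow-up evaluations will be conducted flexibly, adapting to the natural course of participant engagement and clinical needs". The schedule is an aim, "including potential evaluations around 3 months, 6 months, 1 year", continuing to "2 years, within 5 years, and within 10 years", and "the precise timing and frequency of these follow-ups will depend on individual participant availability and consent".

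Section 5 makes the content of each visit optional as well. Assessments are done "as feasible and subject to participant consent and willingness to participate in specific evaluations", and for MRI "The specific imaging modalities used will depend on participant consent and feasibility of each scan".

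No section restricts repeated measures ANCOVA to complete or fixed-time data, and none gives an attendance or dropout rate.

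**The concern.** The justifying sentence follows a pair of methods and, on its natural reading, covers both. For classical repeated measures ANCOVA it is wrong. That method treats time as a factor with the same levels for everyone and works on participants who have a value at every level analysed. A participant with one gap is removed from the whole analysis. Its results are generally safe only if data are missing completely at random.

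For the mixed model the wording is too broad. Likelihood estimation on all available data is valid if data are missing at random given what is in the model, not under any missingness.

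This matters here because gaps arise in three ways: by visit, by assessment and by imaging modality. Visits also adapt to clinical needs, so whether a participant is seen may be related to the outcome. The two methods can therefore analyse different sets of people, yet the text presents them as interchangeable on this point. The study's objectives concern onset, persistence and remission of PTSD, and a set of completers selected on course of illness is a poor basis for those questions.

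**Working it through.** The protocol states no sample size, attendance rate or dropout rate, so there is no figure of its own to reproduce. The numbers below rest on assumed attendance.

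**1. Share of participants kept by a complete-case method**

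Inputs:
- k, the number of follow-ups in the model. Section 3 lists six: 3 months, 6 months, 1 year, 2 years, within 5 years, within 10 years. How many enter any one analysis is not stated, so k runs from 1 to 6.
- p, the chance of attending each follow-up. This is an assumption, as is independence between visits. Everyone is taken to have a baseline.

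Formula: share complete = p^k.

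| p | k = 1 | k = 2 | k = 3 | k = 4 | k = 6 |
|---|---|---|---|---|---|
| 0.95 | 95% | 90% | 86% | 81% | 74% |
| 0.90 | 90% | 81% | 73% | 66% | 53% |
| 0.80 | 80% | 64% | 51% | 41% | 26% |
| 0.70 | 70% | 49% | 34% | 24% | 12% |

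For k = 6: 0.7^6 = 0.118, 0.8^6 = 0.262, 0.9^6 = 0.531.

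**2. When more than half are lost**

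Solving p^k = 0.5 gives p = 0.5^(1/k): 0.50 for k = 1, 0.71 for k = 2, 0.79 for k = 3, 0.84 for k = 4 and 0.89 for k = 6. Most participants are lost only when attendance falls below the value for the number of follow-ups used.

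**3. Dependence between visits**

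If the same people tend to miss visits, the complete share exceeds p^k. At the extreme, where the same people miss every visit, it equals p. At p = 0.8 and k = 6 the share then lies between 26% (independent) and 80% (fully dependent). Gaps in single assessments or scans would lower these figures. The protocol gives nothing with which to quantify that.

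**4. Selection: an illustration**

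A simulation (60 runs, 200 participants, six follow-ups) let dropout in one group depend on the last observed value, which is missing at random. It compared a random-intercept mixed model on all available data with a linear regression restricted to completers. About 54% were complete.

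| Quantity | Truth | Completers only | Mixed model |
|---|---|---|---|
| Baseline group difference | 0 | -0.27 (Monte Carlo SE 0.02) | +0.01 (SE 0.02) |
| Group-by-time slope | -0.10 | -0.098 | -0.102 |

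In this one scenario the completers were a visibly selected group, but the estimated change over time was not distorted.

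**The case against.** The strongest reply is that the justifying sentence follows directly on linear mixed-effects models, itself a plural, and may be meant for those alone. That reading is possible. But the sentence serves as the reason for offering the pair, nothing in it excludes the first method, and even on the narrow reading it leaves out the missing-at-random condition.

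Second, the protocol already offers the suitable method, so the loss arises only if the other branch is taken. That is true and limits the size of the point. It does not make the stated property correct.

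A reader might also infer more than the protocol supports:

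- *That most participants would be discarded.* No attendance rate or number of analysed occasions is given. At 90% attendance with all six follow-ups, 53% are kept; with one follow-up at 80%, 80% are kept. Section 3 calls the visits potential, and nothing says that one model will use all six. Positively correlated attendance would raise the share further.
- *That estimates of change would be biased.* The simulation does not show this. Bias depends on the missingness mechanism, which is unknown.
- *That visits years apart will be pooled as one occasion.* Read literally, the 5-year and 10-year limits contain the earlier visits. In an ascending list they more naturally mean successive later assessments, and the assignment of visits to occasions may properly sit in a statistical analysis plan.
- *That the protocol should already fix the time function, the random effects and a sensitivity analysis for data not missing at random.* Those are details for a statistical analysis plan, and their absence here is no fault.

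**Conclusion.** The statement is wrong as written for classical repeated measures ANCOVA and too broad for the mixed model. If the ANCOVA branch were used, the study could lose a large share of its participants, possibly most: with all six follow-ups required and independent attendance, it would keep between 12% and 53% at attendance of 70% to 90% per visit. With one or two well-attended follow-ups the loss would be modest. All these percentages rest on assumed attendance, not on the documents.

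What does not depend on the assumptions is the mismatch. A method that needs common, complete occasions is offered for visits that are flexible in timing, frequency and content, on a justification it cannot meet. Those it keeps are a selected group unless data are missing completely at random, which is hard to defend when visits follow clinical need and participants' willingness.

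**What to change.** In section 6.1 (2):

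- Name the linear mixed-effects model, using all available visits and actual elapsed time, as the method for longitudinal outcomes.
- Keep repeated measures ANCOVA, if at all, only for comparisons at fixed occasions where data are essentially complete.
- Replace the robustness claim about missing data with: *valid if data are missing at random given the modelled variables*.

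The form of the time term, the random-effects structure and any sensitivity analysis for data not missing at random can be left to the statistical analysis plan.

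The cost is a change of wording and slightly more modelling work. No extra data, visits or procedures are needed.

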# **Study Protocol:**

## **The effects of trauma exposure on the brain, behavior, and cognition: A longitudinal neuroimaging study**

### **1. BACKGROUND**

Posttraumatic stress disorder (PTSD) is a psychiatric condition that can develop following exposure to traumatic events involving a serious threat to life, physical injury, or witnessing the death or suffering of others. Despite the widespread occurrence of trauma in the general population, only a subset of individuals develop PTSD, indicating that individual differences in neurobiological sensitivity and psychological resilience play crucial roles in determining clinical outcomes. Identifying the mechanisms underlying this variability remains a fundamental question in psychiatric neuroscience.

Previous neuroimaging studies have revealed alterations in brain networks involved in emotional regulation, threat detection, and stress reactivity in individuals with PTSD. These studies suggest that PTSD is associated with both functional and structural brain changes. However, most of this work has relied on cross-sectional data, making it difficult to determine whether the observed neural abnormalities precede the development of symptoms, result from trauma exposure, or persist as enduring traits in chronic cases. Without longitudinal evidence, it remains unclear whether these neural signatures represent markers of vulnerability, illness maintenance, or recovery.

The need for longitudinal research is particularly urgent in civilian trauma populations, which have received comparatively less attention than military or disaster-exposed cohorts. In everyday life, individuals are more likely to experience trauma through interpersonal violence, serious accidents, or medical crises rather than through war or large-scale disasters. Nevertheless, most existing PTSD studies have focused on highly specific groups, limiting their applicability to broader civilian populations. Furthermore, developmental aspects of trauma responses remain underexplored. Adolescents and young adults, whose brains are still undergoing rapid maturation, may be particularly vulnerable to long-term neurobiological consequences of trauma exposure, or alternatively, may exhibit unique patterns of resilience.

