## **2. OBJECTIVES OF STUDY**

This naturalistic observational study aims to investigate the biological and psychological mechanisms underlying the development and recovery of PTSD in a civilian sample following exposure to various traumatic events. Through comprehensive longitudinal assessments of brain structure and function, behavior, and cognition in trauma-exposed individuals, the study seeks to identify key factors contributing to individual differences in clinical outcomes. Specifically, the study will examine neuroimaging characteristics, psychosocial influences, peripheral blood-based biomarkers, and genetic predispositions that are associated with the onset, persistence, or remission of PTSD.

The ultimate goal of this study is to elucidate the pathophysiological mechanisms of PTSD and to discover predictive and protective factors that may inform the development of early diagnostic tools and more effective, biologically grounded treatments.

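### Repeated marker-severity associations are planned without separating within-person from between-person association, so the usual single mixed-model slope may not tell a stable marker from one that tracks symptoms

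*Protocol*

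**What the plan says.** Protocol Section 6.1(3) is the only stated analysis that links a marker to severity. It begins: "Correlations between clinical severity, scale scores, and other assessment findings will be examined using Pearson's correlation or Spearman's correlation". It does not say whether these correlations are taken at one visit, on change scores, or over pooled visits. It continues: "To control for potential confounding variables and assess independent relationships", "multiple linear regression or linear mixed-effects models will be used, as appropriate". How the marker is coded or centred, and the random-effects structure, are not stated.

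Section 6.1(2) covers change over time: "To assess longitudinal changes in neuroimaging, clinical, neurophysiological, and neuropsychological measures, repeated measures ANCOVA or linear mixed-effects models will be employed". This concerns the course of each measure.

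Section 1 gives the reason for following people over time. Cross-sectional data cannot show whether abnormalities come before symptoms, follow from trauma, or "persist as enduring traits in chronic cases", and so "it remains unclear whether these neural signatures represent markers of vulnerability, illness maintenance, or recovery". Section 2 seeks factors "associated with the onset, persistence, or remission of PTSD".

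Section 3 applies the baseline procedures at every follow-up and names six possible follow-up times, but leaves timing and number to each participant. Section 5 lists both the PTSD interview and imaging at baseline and follow-up, as far as feasible and consented to.

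**The concern.** A marker measured repeatedly carries two kinds of information about severity. People with higher average marker values may have worse symptoms on average (between-person). A given person's symptoms may also be worse at visits where that person's marker is above its own usual level (within-person). Only the second shows that a marker moves with illness or recovery.

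A correlation at a single visit reflects differences between people. A mixed model with the marker entered as measured returns a weighted average of the two associations. A random intercept handles the dependence between a person's observations but does not separate the two slopes. A marker that is only a stable characteristic can then show a clear association in the longitudinal model and be reported as tracking recovery. If the two associations have opposite signs, both can disappear.

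The distinction at stake is "whether these neural signatures represent markers of vulnerability, illness maintenance, or recovery", which is the one Section 1 gives as the reason for a longitudinal design.

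**Working it through.** **Inputs.** The protocol gives no sample size, effect size, variance or intraclass correlation (ICC), so it has no figure to reproduce. Two inputs come from it: up to 7 visits (baseline plus the six follow-up times in Section 3) and two-tailed 0.05 (Section 6.2). All other values are assumptions.

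**Step 1: what the single slope estimates.** Let the marker be x = b + w, where b is the person's stable level with variance r (the marker ICC) and w is the visit deviation with variance 1−r. Severity has slope βB on b and βW on w, a person effect with variance q (the residual ICC) and visit error with variance 1−q. With m visits per person:

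- variance of the observed person mean: V_M = r + (1−r)/m
- variance within person: V_W = (1−r)(1−1/m)
- slope on the observed mean: βM = [βB·r + βW·(1−r)/m] / V_M
- weights: wB = m·V_M / (1−q+mq) and wW = m·V_W / (1−q)
- share on the between-person part: λ = wB/(wB+wW)
- single slope = λ·βM + (1−λ)·βW

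**Step 2: a purely between-person marker** (βB = 0.5, βW = 0, r = 0.7, q = 0.5).

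| Visits | wB | wW | λ | βM | Single slope |
|---|---|---|---|---|---|
| 2 | 1.133 | 0.6 | 0.654 | 0.412 | 0.27 |
| 3 | 1.2 | 1.2 | 0.5 | 0.4375 | 0.22 |
| 5 | 1.267 | 2.4 | 0.345 | 0.461 | 0.16 |
| 7 | 1.3 | 3.6 | 0.265 | 0.471 | 0.13 |

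For 3 visits: V_M = 0.7 + 0.3/3 = 0.8, wB = 3×0.8/(0.5+1.5) = 1.2, V_W = 0.3×2/3 = 0.2, wW = 3×0.2/0.5 = 1.2, and the slope is 0.5×0.4375 = 0.219. The truth is the same in every row; only attendance changes.

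**Step 3: sensitivity.** With 2, 3 or 5 visits, marker ICC 0.5, 0.7 or 0.9 and residual ICC 0.3 or 0.6, λ runs from 0.15 to 0.91. The single slope for the same marker runs from 0.062 to 0.432. Ordinary regression on pooled visits gives 0.5×r, that is 0.25 to 0.45.

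**Step 4: simulation** (150 people, 3 visits, r = 0.7, q = 0.5, 200 runs per row). Percentages are runs with p < 0.05.

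| True βB, βW | Single slope | Deviation term | Mean term |
|---|---|---|---|
| 0.5, 0 | 0.219 (96.5%) | 0.008 (3.5%) | 0.447 |
| 0, 0.5 | 0.283 (100%) | 0.488 (100%) | 0.057 |
| 0.5, −0.3 | 0.027 (6%) | −0.298 (97.5%) | 0.402 |
| 0.3, 0.3 | 0.303 (100%) | 0.297 (98.5%) | 0.308 |

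The first two rows are opposite truths with similar single slopes. In the third, both associations are hidden. In the fourth, the slopes are equal and the single slope is right. In the third row the formula gives 0.5×0.4 + 0.5×(−0.3) = 0.05, against 0.027 simulated, because the fitted variances absorb some of the misfit and shift the weights.

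**Step 5: does splitting the marker suffice?** No. If marker and severity share a time trend but have no other within-person link, the deviation term without time in the model was falsely significant in 93% of runs. With time added, the rate was 5%. The 93% depends on the assumed trend (a common decline of 0.3 per visit, marker variance 1, reproduces it); a smaller trend gives a lower rate.

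**The case against.** The strongest objection is that the protocol prescribes no single slope. A mixed model holding a person mean and a deviation is still a linear mixed-effects model, so the better analysis already fits the wording, and the correlations could be run on change scores. A separate analysis plan may also settle the parameterisation. This stands in part: a reader might infer that the protocol commits itself to a blended slope, and the text does not support that. What remains is that the only stated marker-severity analysis is directed at confounder control, and the default form of the named model does not answer the question in Section 1. The choice decides which question the coefficient answers, so it is more than a coding detail.

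A reader might also infer that the study will get a wrong answer. That does not follow: with equal slopes the single coefficient is unbiased.

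Section 6.1(2) does model change, and group trajectories bear on Section 1, so the repeated data are not wasted. But item (2) does not link change in a marker to change in severity in the same person.

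Finally, the mean term might be read as showing vulnerability. It cannot. Exposed participants enrol after trauma, so someone ill at every visit carries that illness in the mean. Nor does a same-visit deviation show which came first. Both limits are accepted and shape the fix.

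**Conclusion.** The point holds conditionally. Section 6.1(3) leaves open how repeated marker-severity associations are modelled. If the named mixed model is fitted in its usual form and the within-person and between-person slopes differ, the result cannot tell a stable marker from one that tracks symptoms, and its size depends partly on attendance.

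Under the stated assumptions a purely between-person slope of 0.5 appears as 0.27 with 2 visits and 0.13 with 7, and with 3 visits and 150 people it is significant in 96.5% of runs although the true within-person slope is zero. These figures illustrate the mechanism. They do not predict this study's results, since the protocol supplies neither variances nor effect sizes. This is a change that should be made because it is cheap and serves the stated rationale; it is not a demonstrated error in the plan.

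**What to change.** In Section 6.1(3), state that for any marker measured at two or more visits the association with severity will be estimated in a linear mixed-effects model containing:

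- the participant's own mean of the marker
- the visit's deviation from that mean
- time since baseline or since trauma (time since baseline is defined for both groups)
- the planned covariates

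Add a test of whether the two marker slopes differ. Base any statement that a marker tracks symptom change or recovery on the time-adjusted deviation term. Report the mean term only as a stable between-person association, not as proof of pre-trauma vulnerability or of temporal order. Say also whether the correlations use one visit or change scores, and do not pool visits in them.

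The cost is a few model terms and no new data. The within-person slope is less precise when people have few visits, and participants with one visit do not contribute to it. The mean term is pulled slightly toward the within-person slope when the mean rests on few visits (0.447 instead of 0.5, and 0.057 instead of 0, in the simulation above), which should be acknowledged when it is reported.
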